## Abstract

**Background:**

Gestational diabetes mellitus (GDM) is defined as impaired glucose tolerance with onset or first recognition during pregnancy, which is characterized by an increased insulin resistance. Gestational diabetes mellitus is associated with pregnancy-related maternal and fetal morbidity (both antenatal and perinatal).

Myo-inositol has been suggested to improve insulin resistance in women with polycystic ovary syndrome.

The aim of this study is to examine the impact of myo-inositol supplementation during pregnancy on the incidence of gestational diabetes mellitus.

**Methods:**

We will conduct a single-center, open-label, randomized controlled trial. A total of 160 healthy pregnant women with singleton pregnancy at 11–13^+6^ weeks of gestation will be randomly allocated in two groups: intervention group (*N* = 80) and control group (*N* = 80). The intervention group will receive myo-inositol and folic acid (4000 mg myo-inositol and 400 mcg folic acid daily) from 11 to 13^+6^ weeks of gestation until 26–28 weeks of gestation, while the control group will receive folic acid alone (400 mcg folic acid daily) for the same period of time as intervention group. The primary outcome will be gestational diabetes incidence rate at 26–28 weeks of gestation, according to the results of a 75 g oral glucose tolerance test held at 26–28 weeks of gestation. The secondary outcomes will include fasting blood glucose levels, glycated hemoglobin levels, insulin resistance level (evaluated by homeostasis model assessment of insulin resistance and Matsuda Index), and incidence rate of diet-treated gestational diabetes and diabetes requiring insulin therapy at 26–28 weeks of gestation.

**Discussion:**

This trial will provide evidence for the effectiveness of myo-inositol supplementation during pregnancy in reducing the incidence of gestational diabetes mellitus.

**Trial registration:**

ISRCTN registry: ISRCTN16142533. Registered on 9 March 2017.

## Background

Gestational diabetes mellitus (GDM) is defined as impaired glucose tolerance with onset or first recognition during pregnancy, which is characterized by an increased insulin resistance [1, 2]. The prevalence of that complication is rising worldwide [3]. The onset of GDM is associated with several risk factors such as advanced maternal age, increased body mass index (BMI), ethnic background, and family history or previous history of gestational diabetes [2]. Advancing maternal age and increased prevalence of obesity have contributed to the escalation in rates of GDM. Although the reported rates of GDM imply an incidence that reaches 10% of pregnancies, its prevalence is expected to be higher, almost double, according to the newly proposed criteria for diagnosing GDM [4].

Gestational diabetes mellitus is associated with pregnancy-related maternal and fetal morbidity (both antenatal and perinatal). Maternal hyperglycemia is associated with an excessive increase of fetal weight. Perinatal morbidity is increased due to complications such as fetal macrosomia, shoulder dystocia, birth injuries, neonatal hypoglycemia, and respiratory distress syndrome [5]. Maternal morbidity includes, although not limited to, cesarean delivery, hypertensive disorders, preeclampsia, and predisposition to the development of type 2 diabetes (T2D) later in life [6]. The macrosomic newborns are at increased risk for the onset of obesity, hypertension, and diabetes later in life [7]. The increasing prevalence of fetal and maternal complications related to GDM led to increased awareness of this condition worldwide.

Pregnancy is characterized by insulin resistance. This metabolic state seems to be necessary to ensure a continuous supply of nutrients to the fetus even in conditions of famine. Most pregnant women respond to this effect by increasing insulin release and remain euglycemic. On the other hand, women with GDM are unable to counteract insulin resistance. Insulin-sensitizing factors, such as metformin, have been proposed as a potential treatment to reduce the incidence of GDM in high-risk pregnancies. While metformin initially appeared to be a promising intervention for the prevention of the disease, it does not seem to be as efficacious as expected [8]. The combination of intensive monitoring during the pregnancy course and the use of novel insulin regimens renders possible the effective regulation of blood glucose levels and improves the perinatal outcome. However, the incidence of macrosomia does not appear to be significantly reduced, resulting in a large percentage of macrosomic newborns (15–45%) [9].

It is logical to consider that preventive strategies are better than active response following the presentation of a complication. Safe and effective interventions are, therefore, urgently needed in an attempt to lower the incidence of gestational diabetes or at least the incidence of GDM related morbidity. Such strategies will also benefit health care systems as they could significantly decrease the economic burden of the disease in a national and international setting. Previous studies suggested that inositol may significantly decrease insulin levels in women with polycystic ovary syndrome (PCOS) when administered as one of the two isomer forms, myo-inositol [10] or D-chiro-inositol [11].

Inositol phosphoglycan is an intracellular insulin mediator, which is associated with insulin sensitivity in conditions of insulin resistance, such as T2D [12, 13]. Gestational diabetes mellitus is characterized by increased urinary excretion of inositol phosphoglycan, which shows a positive correlation with blood glucose levels [14, 15]. This observation has also been reported in patients with insulin resistance related to PCOS [16], who have been successfully treated with myo-inositol and folic acid [17]. In a previous study, D’Anna et al. suggested that myo-inositol may actually prevent the occurrence of GDM in PCOS women [18]. The insulin resistance of the syndrome seems to be characterized by a defect in tissue availability or utilization of inositol mediator; therefore, the supplementation of that mediator would improve the intracellular effect of insulin [13, 14, 16, 17]. These findings support the hypothesis that inositol administration could decrease insulin resistance related to GDM. Inositol is considered as a dietary supplement rather than a drug and is present in many foods, such as cereals, corn, legumes, and meat. It is synthesized principally by the liver. To date, a handful of randomized trials have assessed the impact of inositol regimens on the incidence of GDM. Of those, two studies that recruited overweight pregnant women observed > 50% reduction in the incidence of GDM [17, 19], and one study that included obese women observed nearly 60% reduction [20]. Women with polycystic ovarian syndrome may also benefit from inositol supplementation during pregnancy as the incidence of GDM seems to be reduced by more than 60% according to the findings of another study [18]. Results, however, seem to be conflicting in cases with a family history of GDM as D’Anna et al. observed a significant effect [13] whereas Farren et al. did not [21].

This randomized, open-label study is designed to evaluate the impact of myo-inositol supplementation from the first trimester of pregnancy on GDM prevalence. Results of this study will provide evidence regarding the value of myo-inositol as a safe intervention for the prevention of GDM.

## Methods/design

A SPIRIT checklist is available online for this manuscript (Additional file 1).

### Aims

We hypothesize that myo-inositol supplementation from 11 to 13^+6^ weeks of gestation until the time of GDM diagnosis (26–28 weeks of gestation) will reduce the incidence of GDM. To test this hypothesis, we will compare an intervention group and a control group. The intervention group will receive myo-inositol and folic acid, while the control group will receive folic acid alone.

### Design and setting

This is a single-center, open-label, randomized controlled trial, which will be conducted in the First Department of Obstetrics and Gynecology in cooperation with the Diabetes Centre of First Department of Endocrinology in Alexandra Hospital in Athens, Greece. The study aims to enroll 160 healthy pregnant women over a 2-year period. Participants will be randomized, using a 1:1 ratio, to receive either myo-inositol and folic acid (4000 mg myo-inositol and 400 mcg folic acid daily) or folic acid alone (400 mcg folic acid daily). At 11–13^+6^ weeks of gestation and after providing written informed consent, patients will be randomly allocated in two groups until 26–28 weeks of gestation. At the time of study entry, Diabetes Centre of Alexandra Hospital will offer measurements of fasting blood glucose and glycated hemoglobin to all participants of both groups. At 19–20 weeks of gestation, the same measurements will be repeated to all participants. Finally, at 26–28 weeks of gestation, the 2 h 75 g oral glucose tolerance test (OGTT) will be offered for the diagnosis of gestational diabetes [4, 22]. The overall flow of the trial is shown in Fig. 1.

**Fig. 1 Fig1:**
[figure not shown]
Trial protocol flow chart

This trial was approved by the trial center’s ethics committee (Scientific Board of Alexandra Hospital, 28/06/2017, ref.: 520/22-06-2017) and is in accordance with the Declaration of Helsinki concerning Human and Animal Rights. Patient information will be treated confidentially with the use of encrypted individualized numbers. Neither the statistician involved nor the research physicians will have access to these data.

### Participants

Healthy adult pregnant women with singleton pregnancy at 11–13^+6^ weeks of gestation will be held eligible for inclusion in the present study.

Research assistants will discuss the expected outcomes and the potential adverse effects of myo-inositol in Greek or English language. Participants will be given a consent form and separate information sheets including information on the main aspects of the trial. Research assistants will obtain the signed consent form from patients willing to participate in the trial.

### Recruitment procedure

Participants will be informed and recruited at the scheduled appointment for the first trimester ultrasound at Maternal-Fetal Medicine Department of Alexandra Hospital for the measurement of nuchal translucency at 11–13^+6^ weeks of gestation.

Based on a 4-month pilot study, a recruitment rate of 20 patients eligible for the trial per month and 10 consenting patients per month is estimated, achieving adequate participant enrolment to reach the target sample size during the 2-year period of recruitment.

### Inclusion criteria

Patients will be enrolled if they are aged over 18 years old without pre-existing impaired glucose tolerance, have singleton pregnancy, and provide signed informed consent.

### Exclusion criteria

Age under 18 yearsMultiple pregnanciesPre-existing diabetes mellitusConsumption of steroidsHypertensive disordersHypothyroidismPre-existing renal or hepatic impairmentBeta thalassemia carriersVaginal bleeding (e.g., placental abruption)Special diets (e.g., lactose intolerance)Inadequate monitoring during pregnancy

### Interventions

As routine for the geographical area where this study is conducted, the control group will be given 400 mcg of folic acid orally per day, while the intervention group will be given 4000 mg of myo-inositol plus 400 mcg of folic acid per day (2000 mg myo-inositol and 200 mcg folic acid twice daily) from 11 to 13^+6^ weeks of gestation until 26–28 weeks of gestation. At the time of study entry, the Centre of Diabetes of Alexandra Hospital will offer measurements of fasting blood glucose and glycated hemoglobin to all participants of both groups. At 19–20 weeks of gestation, the same measurements will be repeated to all participants. Finally, at 26–28 weeks of gestation, the 2 h 75 g oral glucose tolerance test (OGTT) will be offered for the diagnosis of gestational diabetes [4, 22]. An evaluation of maternal glycemic status will be performed on monthly intervals until delivery and neonates will be followed up until 6 months of life.

Adherence will be monitored at every post-allocation visit by the responsible research physician. The participants must return the bottles at each visit and the physician will count the tablets left in the bottles. Participants with inadequate adherence will be recorded.

The oral combination of myo-inositol and folic acid and the oral tablet of folic acid alone are manufactured by Italfarmaco S.p.A (Milan, Italy).

A timeline of the study procedures is presented in Fig. 2.

**Fig. 2 Fig2:**
[figure not shown]
Time schedule of enrolment, interventions, and assessments

### Randomization and blinding

Allocation sequence will be based on computer-generated randomization that will be organized by an independent research assistant. Allocation concealment will be ensured with the use of sequentially numbered opaque sealed envelopes which will be constructed and secured by an independent research assistant. Complete blinding of the procedure will not be possible, due to limitations of funding which is provided by the investigators only; hence, placebo will not be similar to the administered regimen (myo-inositol). We do acknowledge the limitation of the non-blinding process in our study; however, given the fact that reported outcomes will not be subjective (physician or patient reported) but rather based on actual biochemical data (OGTT), we believe that the lack of blinding will not affect the integrity of our findings. However, both the statistician and the research physicians will be blind to the selection of participants as this will be performed by an independent research assistant.

### Outcome measures

#### Primary outcomes

The primary outcome measure in the trial is gestational diabetes incidence rate at 26–28 weeks of gestation. According to the results of a 75 g oral glucose tolerance test (OGTT) at 26–28 weeks of gestation, gestational diabetes would be diagnosed if one or more values met or exceeded the following levels of glucose: fasting 5.1 mmol/l (92 mg/dl), 1 h post glucose 10.0 mmol/l (180 mg/dl), and 2 h post glucose 8.5 mmol/l (153 mg/dl) [4, 22].

#### Secondary outcomes

Secondary outcome measures include fasting blood glucose levels; glycated hemoglobin levels; insulin resistance level, evaluated by homeostasis model assessment of insulin resistance (HOMA-IR) and Matsuda Index; incidence rate of diet-treated gestational diabetes; and diabetes requiring insulin therapy.
$$ {\displaystyle \begin{array}{l}\mathrm{HOMA}\hbox{-} \mathrm{IR}=\mathrm{Fasting}\ \mathrm{glucose}\ \left(\mathrm{mmol}/\mathrm{L}\right)\times \mathrm{Fasting}\ \mathrm{insulin}\ \left(\mathrm{mIU}/\mathrm{L}\right)/\kern0.5em 22.5\kern0.5em \mathrm{or}\\ {}\mathrm{HOMA}\hbox{-} \mathrm{IR}=\mathrm{Fasting}\ \mathrm{glucose}\ \left(\mathrm{mg}/\mathrm{dL}\right)\times \mathrm{Fasting}\ \mathrm{insulin}\ \left(\mathrm{mIU}/\mathrm{L}\right)/405\end{array}} $$$$ \mathrm{MATSUDA}-\mathrm{I}={10}^4/\surd \left(\mathrm{Fasting}\ \mathrm{glucose}\times \mathrm{Fasting}\ \mathrm{insulin}\right)\times \left(\mathrm{Mean}\ \mathrm{glucose}\times \mathrm{Mean}\ \mathrm{insulin}\right) $$

Maternal hyperglycemia and hyperinsulinemia will be assessed in monthly follow-up visits until delivery as well to determine the impact of myo-inositol on the overall pregnancy course.

Neonatal outcomes (time and mode of delivery, birth weight, admission to a neonatal intensive care unit, perinatal morbidity, perinatal mortality) will be reported as a secondary analysis of our findings in an upcoming paper, following close follow up of neonates up until the age of 6 months.

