### Sample size calculation

Given the lack of previous data in this field, we sought to determine the sample size of our study based on two types of calculations. The largest sample size was finally used to ensure that our study would not be underpowered. The level of statistical significance was set at 0.05 and the power of the study at 0.80 using an 1/1 allocation. In our first attempt, we used the study of Genazzani et al. [10] and calculated the sample size taking into account the fasting insulin levels. The effect size was calculated to be 0.86 and the sample size in each group of 30 women. In the second attempt, we used the decline in the prevalence of GDM that was observed in the study of D’Anna et al. [20] (14 vs. 33.6%). According to the latter sample size calculation, 73 women were needed in each group. With an estimated 10% of patient withdrawal and lost to follow up rates, the final number of enrolled women was estimated to 160 women. Given the relevance of the prevalence of GDM in the latter study to that of the Greek population that is treated in our hospital [23] and other studies in this field that supports an almost 50% reduction in GDM following inositol treatment [16, 24], we chose to include the latter calculation in our study. The G power tool v. 3.1.9.2 was used in all cases.

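### The printed Matsuda formula leaves the OGTT mean product outside the root, so its fasting and post-load terms pull in opposite directions

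*Protocol article*

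**What the plan says.** The protocol article (Secondary outcomes) lists "insulin resistance level, evaluated by homeostasis model assessment of insulin resistance (HOMA-IR) and Matsuda Index" and prints a formula for each index.

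- **HOMA-IR** appears in two versions with units, one for mmol/L (divisor 22.5) and one for mg/dL: "HOMA}\hbox{-} \mathrm{IR}=\mathrm{Fasting}\ \mathrm{glucose}\ \left(\mathrm{mg}/\mathrm{dL}\right)\times \mathrm{Fasting}\ \mathrm{insulin}\ \left(\mathrm{mIU}/\mathrm{L}\right)/405".
- **Matsuda** appears once, without units: "MATSUDA}-\mathrm{I}={10}^4/\surd \left(\mathrm{Fasting}\ \mathrm{glucose}\times \mathrm{Fasting}\ \mathrm{insulin}\right)\times \left(\mathrm{Mean}\ \mathrm{glucose}\times \mathrm{Mean}\ \mathrm{insulin". Written out, this is 10^4/√(fasting glucose × fasting insulin) × (mean glucose × mean insulin).

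Both pairs of brackets are explicit, and no outer bracket encloses the two products. The formula appears nowhere else in the article. The article does not say which direction of the Matsuda index means more resistance.

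**The concern.** The root applies to the fasting product only. By the normal order of operations, the OGTT mean product then sits in the numerator. The HOMA-IR lines just above treat a larger glucose × insulin product as more resistance. The printed Matsuda index divides by the root of one such product and multiplies by the other, so it does not measure one thing in one direction.

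Insulin sensitisation is the rationale for the trial (Background, Discussion), and this is one of two indices named for insulin resistance. If the printed form were coded, a treatment effect on post-load glucose and insulin would move the index one way and an effect on fasting values would move it the other way. A real benefit could be diluted or could appear with the wrong sign. Readers who recompute the index from the article would have the same problem.

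**Working it through.** **Inputs.** The formulas are those under Secondary outcomes. The article gives no glucose or insulin data for evaluating them, so the profiles below are assumptions, in mg/dL and mIU/L. FG and FI are fasting glucose and insulin; MG and MI are the OGTT means.

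**Stated figures.** The article gives no numerical result for the Matsuda index, so there is none to reproduce. The companion formulas agree with each other: 22.5 × 18 = 405, where 18 is the mmol/L to mg/dL factor implied by the two constants. The sample size ("14 vs. 33.6%). According to the latter sample size calculation, 73 women were needed in each group") does not use the index. A two-proportion calculation with two-sided 0.05, power 0.80 and no continuity correction returns 73 per group.

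**Two readings.**

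- As printed: P = 10^4/√(FG × FI) × (MG × MI)
- All under the root: R = 10^4/√(FG × FI × MG × MI)

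**Step 1: two contrasting women (assumed).**

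| FG / FI / MG / MI | HOMA-IR | R | P |
|---|---|---|---|
| 80 / 6 / 110 / 40 | 480/405 = 1.19 | 10^4/√(480 × 4,400) = 6.88 | 10^4/√480 × 4,400 = 2,008,316 |
| 95 / 15 / 150 / 100 | 1,425/405 = 3.52 | 10^4/√(1,425 × 15,000) = 2.16 | 10^4/√1,425 × 15,000 = 3,973,597 |

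R falls as HOMA-IR rises. P rises, so the order of the two women reverses.

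**Step 2: one component at a time, from an assumed middle profile 85 / 10 / 130 / 60.**

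| Change | R | P |
|---|---|---|
| None | 3.88 | 2,675,378 |
| Fasting insulin doubled | 2.75 | 1,891,778 |
| OGTT mean insulin doubled | 2.75 | 5,350,756 |
| Both doubled | 1.94 | 3,783,556 |

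R falls in every row. P falls, rises and rises.

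**Step 3: the general condition.** Multiply the fasting product by a and the mean product by b.

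- R changes by the factor 1/√(ab), so it falls whenever either product worsens and the other does not improve.
- P changes by the factor b/√a, so it rises only if b > √a. With a = b > 1 the factor is √a, so P rises.
- P can also fall when both products worsen. With a = 4 and b = 1.5 (85 / 40 / 130 / 90) the factor is 1.5/2 = 0.75, and P falls from 2,675,378 to 2,006,533. R falls from 3.88 to 1.59.
- For the pair in step 1, a = 1,425/480 = 2.97 and b = 15,000/4,400 = 3.41. The factor is 3.41/1.72 = 1.98, which matches 3,973,597/2,008,316.

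The opposing directions follow from the algebra and do not depend on the assumed profiles. The profiles only show the size.

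**Step 4: units.** In R, moving from mg/dL to mmol/L divides both glucose terms by 18 and so multiplies the index by √(18 × 18) = 18 (middle profile: 3.88 becomes 69.9). If one unit is used throughout, this is the same constant for every woman.

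**The case against.** The strongest reply is that this is notation and not a planned analysis. The root sign has no overbar, both products follow it on one line, and the authors may well have meant it to cover everything. The index is named, and literal coding would give values in the millions, which a statistician would probably notice. No analysis code is shown. All of this is fair, and it bears on severity. It does not remove the defect: the brackets are the only marker of the root's scope, they close too early, and no other text corrects them. A stated outcome formula that computes the wrong quantity is an error in the document, not a detail left to an analysis plan.

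The illustrative values are assumed. That objection touches the sizes in steps 1 and 2 but not the algebra in step 3.

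Four stronger inferences are tempting, and the document does not support them:

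- **That the printed index simply rises with insulin resistance.** It does so only when b > √a. If only the fasting product worsens, it falls. An effect of myo-inositol mainly on fasting values would therefore move it up.
- **That the missing units could distort the comparison by a factor of 18.** A common factor leaves ratios, ranks and the parametric and non-parametric tests unchanged. Only mixing units between women would matter, and nothing in the article suggests that.
- **That the OGTT means are to be taken over particular insulin sampling times.** The article gives fasting, 1 h and 2 h thresholds for glucose only, and no insulin sampling times.
- **That the trial's result on this outcome will be reversed.** This needs the printed form to be the one coded, which the document does not show.

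**Conclusion.** The formula is wrong as printed. Its fasting and post-load halves act in opposite directions, so it is coherent neither as a resistance nor as a sensitivity measure. It reverses the order given by the form with everything under the root whenever both products worsen and the mean product grows by more than the square root of the fasting product's growth. Equal proportional worsening is one such case. In the assumed pair, 6.9 against 2.2 becomes 2.0 against 4.0 million.

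Two assumptions underlie this: the printed brackets are read literally, and the form with everything under the root is what the authors intend. The article does not print that form.

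Severity is moderate to minor. One of two measures of one secondary outcome is affected. The primary outcome (GDM by OGTT thresholds), HOMA-IR and the sample size do not use the formula.

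**What to change.** In the protocol, under Secondary outcomes:

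1. Add one outer bracket: Matsuda index = 10^4/√[(fasting glucose × fasting insulin) × (mean OGTT glucose × mean OGTT insulin)].
2. State one glucose unit, used for all women, so that absolute values can be read and compared.
3. State that lower values mean more insulin resistance, the opposite direction to HOMA-IR.

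Then confirm that the analysis code uses this form. If it does, this is a correction of the printed text only. If it does not, correct the code before the outcome is analysed. The cost is one line of text and one check of the code. Sample size, visits and data collection do not change.
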